## 7.5. Subsequent treatment

Treatment after discontinuation of study treatment is at the discretion of the patient's clinician.

## ALT GIST

### 8. ASSESSMENT PLAN

#### 8.1. Schedule of assessments

Assessments must be completed within 3 days of the assessment due date (unless otherwise specified in the footnotes)

**ARM A IMATINIB ALONE** NB: 1 cycle in continuous treatment arm = 8 weeks of imatinib (56 days)

| Parameter                                        | Screening/
Baseline
(28 days prior to
randomisation) | Cycle 1        |         | Cycle 2 |         | Cycle 3 |         | Cycle 4 and ongoing
cycles         | 30 day
safety
assessment | Follow-up (12 weekly)                          |
|--------------------------------------------------|---------------------------------------------------------------|----------------|---------|---------|---------|---------|---------|---------------------------------------|--------------------------------|------------------------------------------------|
|                                                  |                                                               | Wk 1D1         | Wk 4 D1 | Wk 1D1  | Wk 4 D1 | Wk1 D1  | Wk 4 D1 | Wk1 D1                                |                                |                                                |
| Informed consent                                 | x a                                                |                |         |         |         |         |         |                                       |                                |                                                |
| Pregnancy test                                   | x                                                             | x d |         |         |         |         |         |                                       |                                |                                                |
| Clinical assessment b                 | x                                                             | x              | x       | x       | x       | x       | x       | x                                     |                                |                                                |
| Mutation status if not
previously determined  | x c                                                |                |         |         |         |         |         |                                       |                                |                                                |
| Biochem e                             | x                                                             | x d | x       | x       | x       | x       | x       | x                                     |                                |                                                |
| Haem f                                | x                                                             | x d | x       | x       | x       | x       | x       | x                                     |                                |                                                |
| Dipstick urine g                      | x                                                             | x              |         | x       |         | x       |         | x                                     |                                |                                                |
| ECG                                              | x                                                             |                |         |         |         |         |         |                                       |                                |                                                |
| Imatinib plasma level h               |                                                               |                | x       |         | x       |         |         |                                       |                                |                                                |
| Blood for translational
research i | x                                                             | x              | x       |         | x       |         |         | x
C4 Wk1 D1 only
C8 Wk1 D1 only |                                | x
At relapse                                |
| Adverse event assessment                         |                                                               | x              | x       | x       | x       | x       | x       | x                                     | x                              |                                                |
| CT scan j                             | x (21 days)                                                   |                |         | x       |         | x       |         | x                                     |                                | x
Continued as per the
protocol until PD |

a: up to 90 days prior to randomisation

b: clinical assessment including vital signs, blood pressure, physical examination, ECOG PS,

c: analysis of tumour mutation status if not previously known does not need to be completed prior to randomisation

d: if screening bloods and urine tests are performed within 14 days prior to randomisation baseline bloods and urine are not required to be repeated

e: biochemistry including serum creatinine, urea, LFT, TFT, calcium, magnesium, phosphate. INR should be checked at baseline and then as clinically indicated

f: full blood count including differential cell count

g: dipstick urinalysis using standard urine test strip is required on D1 of each cycle. If abnormal, further investigations should be conducted as clinically appropriate

h: blood collected for drug (imatinib) level testing. Refer to Biological Sampling Handbook for details of collection and processing. Documentation of compliance with treatment during the preceding cycle should be documented in the eCRF

i: blood for **optional** translational research will be collected at these timepoints. Refer to Biological Sampling Handbook for details of collection and processing

j: for the first 12 months, CT scans are performed 8 weekly from randomisation after which CT scans are performed 12 weekly. Imaging of the brain should be undertaken if clinically indicated. CT scans should continue as per the protocol until PD

# ALT GIST

## ARM B IMATINIB ALTERNATING WITH REGORAFENIB

NB: 1 cycle in alternating arm = 21-25 days of imatinib, 3-7day washout, 21 days of regorafenib, 7 day washout

| Parameter                                        | Screening/
Baseline
(28 days prior
to
randomisation) | Randomis-
ation                                                                                                                                                                                                                           | Cycle 1        |                            |                |                      | Cycle 2        |                            |                |                      | Cycle 3            | Cycle 4 and
ongoing cycles      | 30 day safety
assessment | Follow-up
(12 weekly) |
|--------------------------------------------------|------------------------------------------------------------------|----------------------------------------------------------------------------------------------------------------------------------------------------------------------------------------------------------------------------------------------|----------------|----------------------------|----------------|----------------------|----------------|----------------------------|----------------|----------------------|--------------------|------------------------------------|-----------------------------|--------------------------|
|                                                  |                                                                  |                                                                                                                                                                                                                                              | Wk1
D1      | Last day
of
Imatinib | Wk5
D1      | Last day
of Regor | Wk1
D1      | Last day
of
Imatinib | Wk5
D1      | Last day
of Regor | Wk1 D1 &
Wk5 D1 | Wk1 D1                             |                             |                          |
| Informed consent                                 | x a                                                   | If patient is
on Imatinib
therapy for
longer than
21 days
prior to
randomisati
on a
washout
must occur.
Imatinib
must stop
for a
minimum of
3 days prior
to starting
regorafenib
on D29 . |                |                            |                |                      |                |                            |                |                      |                    |                                    |                             |                          |
| Pregnancy test                                   | x                                                                |                                                                                                                                                                                                                                              | x d |                            |                |                      |                |                            |                |                      |                    |                                    |                             |                          |
| Clinical assessment b                 | x                                                                |                                                                                                                                                                                                                                              | x              |                            | x              |                      | x              |                            | x              |                      | x                  | x                                  |                             |                          |
| Additional monitoring
-BP                     |                                                                  |                                                                                                                                                                                                                                              |                |                            | x m |                      | x m |                            | x m |                      |                    |                                    |                             |                          |
| Mutation status if not
previously determined  | x c                                                   |                                                                                                                                                                                                                                              |                |                            |                |                      |                |                            |                |                      |                    |                                    |                             |                          |
| Biochem e                             | x                                                                |                                                                                                                                                                                                                                              | x d |                            | x              |                      | x              |                            | x              |                      | x                  | x                                  |                             |                          |
| AST, ALT and bilirubin h              |                                                                  |                                                                                                                                                                                                                                              |                |                            | x h | x h       |                |                            | x h | x h       |                    |                                    |                             |                          |
| Haem f                                | x                                                                |                                                                                                                                                                                                                                              | x d |                            | x              |                      | x              |                            | x              |                      | x                  | x                                  |                             |                          |
| Dipstick urine g                      | x                                                                |                                                                                                                                                                                                                                              | x              |                            |                |                      | x              |                            |                |                      | x
Wk1 D1 only   | x                                  |                             |                          |
| ECG                                              | x                                                                |                                                                                                                                                                                                                                              |                |                            |                |                      |                |                            |                |                      |                    |                                    |                             |                          |
| Imatinib plasma level i               |                                                                  |                                                                                                                                                                                                                                              |                | x                          |                |                      |                | x                          |                |                      |                    |                                    |                             |                          |
| Regorafenib plasma
level j         |                                                                  |                                                                                                                                                                                                                                              |                |                            |                | x                    |                |                            |                | x                    |                    |                                    |                             |                          |
| Blood for translational
research k | x                                                                |                                                                                                                                                                                                                                              | x              | x                          |                | x                    |                | x                          |                | x                    |                    | x
C4 Wk1 D1 &
C8 Wk1 D1 only |                             | x
At relapse          |
| Adverse event
assessment                      |                                                                  |                                                                                                                                                                                                                                              | x              |                            | x              |                      | x              |                            | x              |                      | x                  | x                                  | x                           |                          |
| CT scan l                             | x
(21 days)                                                   |                                                                                                                                                                                                                                              |                |                            |                |                      | x              |                            |                |                      | x
Wk1 D1 only   | x                                  |                             | x
Until PD            |
| PET Scan n                            |                                                                  |                                                                                                                                                                                                                                              |                |                            |                |                      |                | x                          | x              |                      |                    |                                    |                             |                          |
| -Imatinib washout
or PET Scan n    |                                                                  |                                                                                                                                                                                                                                              |                |                            |                |                      |                |                            |                |                      |                    |                                    |                             |                          |
| -Regorafenib washout                             |                                                                  |                                                                                                                                                                                                                                              |                |                            |                |                      |                |                            |                | x                    | x
Wk1 D1 only   |                                    |                             |                          |

a: up to 90 days prior to randomisation

b: clinical assessment including vital signs, blood pressure, physical examination, ECOG PS

c: analysis of tumour mutation status if not previously known does not need to be completed prior to randomisation

d: if screening bloods and urine test are performed within 14 days prior to randomisation baseline bloods and urine tests are not required to be repeated

e: biochemistry including serum creatinine, urea, LFT, TFT, calcium, magnesium, phosphate. INR should be checked at baseline and then as clinically indicated

f: full blood count including differential cell count

g: dipstick urinalysis using standard urine test strip is required on D1 of each cycle. If abnormal, further investigations should be conducted as clinically appropriate

# ALT GIST

h: Liver function testing must also be performed weekly in the alternating treatment arm during regorafenib use for the first 2 cycles. AST, ALT and bilirubin must be monitored weekly during regorafenib use for the first 2 cycles of the patient taking regorafenib. Site or local laboratory may be used.

i: blood collected for drug (imatinib) level testing. Refer to Biological Sampling Handbook for details of collection and processing. Documentation of compliance with treatment during the preceding cycle should be documented in the eCRF

j: blood collected for drug (regorafenib) level testing. Refer to Biological Sampling Handbook for details of collection and processing. Documentation of compliance with treatment during the preceding cycle should be documented in the eCRF

k: blood for **optional** translational research will be collected at these timepoints. Refer to Biological Sampling Handbook for details of collection, processing and storage

l: for the first 12months, CT scans are performed 8 weekly from randomisation after which CT scans are performed 12 weekly. Imaging of the brain should be undertaken if clinically indicated. CT scans should continue as per the protocol until PD

m: weekly blood pressure measurements are required from the commencement of regorafenib in cycle 1 until the completion of cycle 2.

n – only in those Arm B patients enrolled in the PET substudy. Patients randomised to have two scans and timing is based on a second randomisation - either PET scans during imatinib washout period, or regorafenib washout period. Depending on allocated arm, PET scans to be performed at the completion of regorafenib or imatinib tablets (or up to 2 days prior) and before the commencement of the subsequent imatinib or regorafenib cycle (or up to 2 days prior). These scans are to be performed in Cycle 2 at the earliest or in a subsequent cycle (at the first opportunity after a complete cycle of treatment with no dose modifications is given).

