## NOTE:

Cycles are 8 weeks (56 days) in length for both arms.

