# ALT GIST

This combination of imatinib, regorafenib and intervening washout periods will constitute 1 cycle of study treatment (imatinib plus washout period 28 days in total; regorafenib plus washout period 28 days in total; cycle duration 8 weeks (56 days) in total). See diagram below.

It is recommended that regorafenib should be taken orally at the same time each day (preferably after breakfast) and the tablets should be swallowed whole with water after a light low fat meal. The prescribed dose of imatinib should be taken orally, with a meal and a large glass of water to minimise the risk of gastrointestinal disturbances

Missed or vomited tablets cannot be compensated for by treatment at a later date and/or time.

[figure not shown]

Even in participants with a complete response, treatment will continue until progressive disease (PD) or prohibitive adverse events are documented. Participants who cease treatment after receiving at least 2 years of therapy from the time of commencing treatment will not be considered to have failed treatment for toxicity reasons. Surgery will be permitted for participants whose cancer becomes operable during trial treatment at the discretion of the treating team, and participants will be able to continue on study treatment and will continue to be followed for progression free survival post operatively. For patients undergoing surgery, regorafenib should be ceased at least 2 weeks prior to surgery, and recommenced on the basis of clinical judgement. During this period, imatinib could be administered until surgery and for the first 2 weeks after surgery regardless of the study Arm allocation,

Treatment after progression will be according to clinician preference and local institutional guidelines. Crossover from either arm to single agent regorafenib will not be permitted as part of the study.

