#### **8.2.2. During treatment**

- Clinical assessment (including vital signs, blood pressure, physical examination, ECOG PS, adverse event monitoring), full blood count (including differential cell count), biochemistry (including serum creatinine, urea, LFT, calcium, magnesium, phosphate) to be performed for ARM A at the beginning of each cycle and at C1, C2 and C3 Wk 4 D1, for ARM B at the beginning of each cycle and at C1, C2 and C3 Wk 5 D1
- All participants who are on regorafenib should have their blood pressure monitored weekly from the commencement of regorafenib in cycle 1 until the end of cycle 2. During this time, participants must attend the clinic weekly for their blood pressure to be taken. Alternatively, the weekly blood pressure measurements can be done by GPs, or using home blood pressure monitors if available. Blood pressure readings collected by the patient at home or by their GP will need to be communicated to the study site for appropriate management. Recommendations for anti-hypertension management will be provided in the Study Manual.
- Liver function testing must also be performed weekly in the alternating treatment arm (Arm B) during regorafenib use for the first 2 cycles. INR should be checked at baseline and then as clinically indicated.
- Dipstick urinalysis using standard urine test strip is required on day 1 of each cycle. If abnormal, further investigations should be conducted as clinically appropriate.
- For patients on Arm A blood collection for drug (imatinib) level testing to be performed on cycle 1 week 4 and cycle 2 week 4. For patients on the alternating regimen (Arm B) blood collected for drug (imatinib) level testing to be performed on cycle 1, on last day of imatinib administration and cycle 2 on last day of imatinib administration. Blood collected for drug (regorafenib) level testing to be performed on cycle 1 week 7 (on last day of regorafenib) and cycle 2 week 7 (on last day of regorafenib).
- Blood for translational research will be collected at the following timepoints;
  - Baseline/screening
  - C1 Wk1 D1 (prior to the commencement of study treatment, Baseline)
  - For Arm A: C1 Wk4 and C2 Wk4.

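### The compliance record tied to the plasma drug levels refers to the preceding cycle, which misses the doses that determine each level

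*Protocol*

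**What the plan says.** The note under the protocol's Study Schema sets the cycle: "Cycles are 8 weeks (56 days) in length for both arms". Section 7.1 repeats this for the alternating arm ("cycle duration 8 weeks (56 days) in total"), and the heading of the Arm B schedule in section 8.1 lists the contents: "1 cycle in alternating arm = 21-25 days of imatinib, 3-7day washout, 21 days of regorafenib, 7 day washout".

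Section 8.2.2 places the plasma levels inside the first two cycles. In Arm A there is "blood collection for drug (imatinib) level testing to be performed on cycle 1 week 4 and cycle 2 week 4"; the Arm A table puts these draws at Wk 4 D1. In Arm B, imatinib is sampled on "cycle 1, on last day of imatinib administration and cycle 2 on last day of imatinib administration". Regorafenib is sampled in week 7 of cycles 1 and 2, on the last day of each regorafenib course. No plasma level is scheduled after cycle 2.

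The compliance instruction attached to these samples is the same in Arm A footnote h and in Arm B footnotes i and j: "Documentation of compliance with treatment during the preceding cycle should be documented in the eCRF". The same footnotes send details of collection and processing to the Biological Sampling Handbook, which is not at hand.

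Section 3 lists the relation between study endpoints and the drug levels (imatinib in Arm A, both drugs in Arm B) among the tertiary and correlative objectives.

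**The concern.** A level drawn at the end of a drug block, or in week 4 of continuous dosing, reflects the tablets taken in that block up to the draw. Adherence is needed for that window if a low level is to be read as low exposure on full dosing rather than as missed tablets. The footnotes ask for a different window, the cycle before.

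At stake is the exploratory analysis that relates levels to endpoints. It will be small, with 22 control and 38 alternating patients planned (section 13.1), so a few levels lowered by missed doses could carry weight. The protocol itself asks for compliance alongside each level, so this is a stated rule that points at the wrong doses, not a detail left for the analysis plan.

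**Working it through.** The protocol gives no figure to reproduce; the check is day arithmetic on its own schedule.

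**Inputs**
- Cycle length: 56 days (Study Schema note; section 7.1).
- Arm B: imatinib from day 1 to day L, with L between 21 and 25; regorafenib on days 29 to 49 of the cycle, since 28 + 21 = 49 (section 7.1).
- Arm A: continuous imatinib; Wk 4 D1 is day 22 of the cycle, since 3 × 7 + 1 = 22.
- Imatinib taken before randomisation counts within cycle 1 (Study Schema note), so it does not supply an earlier cycle.
- No treatment delays. A delay between the last covered dose and the draw would lengthen the gaps below.

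**Cycle 1 draws**

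| Draw | Day | Preceding cycle |
|---|---|---|
| Arm A imatinib | 22 | none |
| Arm B imatinib | 21 to 25 | none |
| Arm B regorafenib | 49 | none |

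Three of the six planned draws have no window to record at the time of sampling.

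**Cycle 2 draws** (preceding cycle = days 1 to 56)

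- *Arm B imatinib.* Draw day = 56 + L2, that is day 77 to 81. Last covered imatinib dose = day L1, that is day 21 to 25. Gap = 56 + L2 − L1. Smallest: 56 + 21 − 25 = 52 days. Largest: 56 + 25 − 21 = 60 days. None of the 21 to 25 imatinib doses of cycle 2 is covered.
- *Arm B regorafenib.* Draw day = 56 + 49 = 105. Last covered regorafenib dose = day 49. Gap = 105 − 49 = 56 days. None of the 21 regorafenib doses of cycle 2 is covered.
- *Arm A imatinib.* Draw day = 56 + 22 = 78. The window ends on day 56. If the draw precedes that day's dose, the uncovered doses are those on days 57 to 77, that is 78 − 57 = 21. Section 8.1 allows 3 days either way, which gives 75 − 57 = 18 to 81 − 57 = 24 doses.

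**Does a later entry close the gap?** Read literally, the entry made with a cycle 2 sample documents cycle 1, so cycle 1 compliance does reach the eCRF in retrospect. It does so for the whole cycle. For an Arm A draw on day 22 that mixes the 21 doses before the draw with the 56 − 21 = 35 from the draw day onwards. For cycle 2, the matching entry would need a cycle 3 sample, and none is scheduled. The footnotes therefore never reach the doses behind the cycle 2 levels.

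**The case against.** Four points on the other side deserve weight.

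1. *Other adherence records exist.* A reader might infer that a low level cannot be told from missed tablets, or that the analysis cannot be adjusted for adherence. The protocol does not support that. Section 12.3 requires pharmacies to record drug dispensed and returned for each patient. Section 13.3 plans a dose-intensity analysis of both drugs after 15 experimental-arm patients have had at least two cycles, which needs dose data for the cycles in which levels are drawn. The retrospective cycle 1 entry adds to this. These sources may give adherence by period. However, none is stated to cover the last doses before a draw, and the section 13.3 analysis concerns Arm B only. In Arm A, dosing runs on past a mid-cycle draw, so a return count need not separate doses before it from doses after it.

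2. *The protocol sometimes uses the word cycle for a single-drug period*, for instance in Arm B footnote n. A site could then take the preceding cycle to be the course just finished, which in Arm B is the right window. This shows that the wording is ambiguous, but it does not rescue it. It conflicts with the formal 56-day definition and does not fit a week 4 draw in Arm A. Taken literally, the single-drug period before the current one in Arm B is the other drug's block, and the cycle 1 imatinib draw still has none.

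3. *The Biological Sampling Handbook may already ask for the time of the last dose.* That cannot be known from the protocol, so its absence is not claimed here. The eCRF instruction in the protocol would still name the wrong window.

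4. *The objective is exploratory and no exposure-endpoint model is specified.* This stands, and it limits the importance of the point.

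**Conclusion.** The point holds as a wording error in a data-collection rule, of low priority. Under the protocol's own 56-day cycle, the compliance window tied to the plasma levels is empty for the three cycle 1 draws and contains none of the current-block doses for the three cycle 2 draws. The last covered dose of the sampled drug is 52 to 60 days (imatinib) or 56 days (regorafenib) before the Arm B cycle 2 draws; in Arm A, everything from day 57 to the week 4 draw is outside it.

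These figures assume the formal meaning of cycle and dosing without delay. The sample-linked record is poorly suited to interpreting low levels, but adherence by period may be partly recoverable from other sources. The effect is confined to the exploratory relation of drug levels to endpoints. The primary endpoint, the secondary endpoints and the sample size are unaffected.

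**What to change.** Reword Arm A footnote h and Arm B footnotes i and j in section 8.1, and the matching eCRF field, so that the record is compliance with the sampled drug from the start of the current drug block up to the draw (in Arm A, from the start of the current cycle). Add date and time of the last dose before the draw if the Biological Sampling Handbook does not already capture it.

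The cost is three footnotes and one eCRF field definition. No visit or blood draw is added, and treatment is not changed.
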